After the completion of the 3 month hemodialysis run in phase, patients will be randomized to either to a further 3 months of hemodialysis or 3 months of hemofiltration. The starting prescription for hemofiltration will be enough replacement fluid (Hemosol) to achieve a daily (6 days/week) treatment Kt/V of 0.50 (±0.05). Each treatment will take approximately 2-2.5 hours and will occur during the day in centre. Remaining in-centre for the duration of the study avoids the potential bias of typically lower blood pressures at home compared to the clinic environment. The starting prescription for hemodialysis will be unchanged from the preceding 3 months (3 days/week, approximately 3.5-4 hours per treatment). Each patient will undergo measurement of their extracellular fluid volume using bioelectrical impedance, sympathetic nervous system activity using microneurography and ambulatory 24-hour blood pressure measurements (during an off treatment day) prior to the start of and at the end of this 3 month phase. Additionally, each patient will have the standard laboratory investigations repeated on the first Wednesday/Thursday of the month. The nurses will document vitals pre and post each treatment session. Medications, and any adverse events including hospitalizations will be reassessed at the time of monthly blood work.

After completing the 3 months of hemofiltration or hemodialysis, patients will then switch treatment modality for a further 3 months. The same protocol will be followed for laboratory investigations, assessment of vitals, medications and adverse events as during the preceding 3 months. Repeat extracellular fluid volume measurement, muscle sympathetic nerve activity and ambulatory blood pressure recordings will be completed at the end of the study.

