**2.9a BLOOD PRESSURE MEASUREMENTS**

Blood pressure will be measured pre and post dialysis as recommended by the Canadian Hypertension Society (www.hypertension.ca). Briefly, the patient will have their back supported, feet on the floor and will sit quietly for 5 minutes. The arm will be supported and a mercury sphygmomanometer will be used*.* An appropriate sized cuff will be placed at the level of the heart and inflated to 20mmHg above the level at which the radial pulse disappears. Phase I Korotkoff, appearance of first sound, will be taken as the systolic blood pressure and phase V Korotkoff, disappearance of sound, will be taken as the diastolic blood pressure. Two measurements will be taken and averaged. Patients will be discouraged from using alcohol, caffeine, or tobacco within one hour of BP measurement. The measurements will be taken in the arm opposite to the one with a functioning access (if a central venous catheter is in place, the non-dominant arm will be used) prior to needle insertion for the hemodialysis/hemofiltration treatment.

Ambulatory blood pressures will be performed with a portable oscillometric recorder (Spacelabs 90207). Recordings will begin after the completion of hemodialysis and hemofiltration and will continue for a 44 hour period (the time between treatments) on three different occasions (at the time of randomization, after the first 3 months of the cross-over phase and again at study completion). The pressure will be measured every 30 minutes. The most appropriate cuff will be selected from the 4 sizes supplied by the manufacturer Sleep times will be determined from patient’s diaries. Nocturnal hypertension will be defined as the absence of a decrease of blood pressure during sleep by 10% compared to the awake period. If fewer than 75% of the potential readings are recorded or if more than 90 minutes lapses without a valid blood pressure recording, the ambulatory session will be repeated in 7 days.

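### The ambulatory blood pressure recording has two different windows, no stated place in the treatment week, and a 7-day repeat that can fall after the change of modality

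*Protocol*

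**What the plan says.** Section 2.9 of the protocol calls for "ambulatory 24-hour blood pressure measurements (during an off treatment day) prior to the start of and at the end of this 3 month phase". Section 2.9a, which governs the same recordings, says: "Recordings will begin after the completion of hemodialysis and hemofiltration", and that they "will continue for a 44 hour period (the time between treatments) on three different occasions". The three occasions are randomization, the end of the first 3 months of the crossover phase, and study completion. Readings are taken every 30 minutes.

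Section 2.9a also has a validity rule. If fewer than 75% of the possible readings are obtained, or more than 90 minutes pass without a valid one, "the ambulatory session will be repeated in 7 days".

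The schedules are in section 2.9. Hemodialysis is given "3 days/week, approximately 3.5-4 hours per treatment". Hemofiltration is set to reach "a daily (6 days/week) treatment Kt/V of 0.50", in daytime sessions of about 2 to 2.5 hours. After the first 3 months, "patients will then switch treatment modality for a further 3 months". No washout is stated, nor any delay of the switch while a failed recording is repeated. Amendment #4 replaces hemofiltration with daily hemodialysis and gives no session length or weekly frequency.

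**The concern.** Staff cannot follow both sections. The choice of window sets how many readings make a recording valid. It can also change the dipping classification, because 44 hours can cover more than one sleep period.

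Section 2.9a treats 44 hours as the interval between treatments without distinguishing the two modalities, whose weekly rhythms are very different. A coordinator who starts the recorder after an arbitrary hemofiltration session will usually find the next session falling inside the window.

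The repeat rule is a separate problem. The recordings sit at the boundaries between periods, and a recording moved 7 days later may be made on the other modality. Section 2.4 counts ambulatory monitoring among the measures unlikely to be affected by knowledge of treatment in an unblinded trial. With 20 patients and three recordings each, a few recordings made on the wrong modality would weaken that protection.

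**Working it through.** **Inputs.** From section 2.9: hemodialysis 3 days a week, 3.5 to 4 h per session; hemofiltration 6 days a week, 2 to 2.5 h per session. From section 2.9a: a reading every 30 minutes, the 75% rule, the 90-minute rule and the 7-day repeat. Assumption: sessions start at the same hour each treatment day.

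**Step 1: reproduce the 44 hours.** Gap = time between session starts minus session length.

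| Modality | Usual gap | Longest weekly gap |
|---|---|---|
| Hemodialysis, 3 a week | 48 − 4 = 44 h to 48 − 3.5 = 44.5 h (twice a week) | 72 − 4 = 68 h to 72 − 3.5 = 68.5 h (once) |
| Hemofiltration, 6 a week | 24 − 2.5 = 21.5 h to 24 − 2 = 22 h (five times a week) | 48 − 2.5 = 45.5 h to 48 − 2 = 46 h (once) |

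The protocol's figure reproduces as the usual hemodialysis gap. It is not the usual hemofiltration gap.

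**Step 2: which gaps can hold a treatment-free window.** On hemodialysis, all 3 weekly gaps hold either 24 h or 44 h. On hemofiltration, 1 of 6 holds either. Section 2.9 requires an off-treatment day but attaches that to 24 h. Section 2.9a requires 44 h and names no day.

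**Step 3: effect on the validity rule.** 44 h × 2 readings an hour = 88, and 75% of 88 = 66. For 24 h, 24 × 2 = 48, and 75% of 48 = 36.

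**Step 4: room for the repeat.** To finish before the switch, the first attempt must start at least 7 days plus one window before it:

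- 44-h window: 7 × 24 + 44 = 212 h = 8.8 days, so about 9 days.
- 24-h window: 7 × 24 + 24 = 192 h = 8 days.

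The protocol states no such lead time.

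**Step 5: which recordings are exposed.**

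- Randomization: all patients are on hemodialysis in the run-in. A repeat may fall on another modality only in those allocated to hemofiltration first.
- Middle recording: every patient then changes modality, so all are exposed.
- Study completion: no crossover follows. A late repeat falls after the study, on whichever modality the patient then chose (section 2.14).

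**Step 6: how often a repeat might be needed.** The documents give no failure rate. With readings 30 minutes apart, three consecutive failures exceed 90 minutes. The chance of at least one such run, if readings fail independently at an assumed rate, is:

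| Assumed failure rate | 44-h window (88 readings) | 24-h window (48 readings) |
|---|---|---|
| 2% | 0.07% | 0.04% |
| 5% | 1.0% | 0.6% |
| 10% | 7.5% | 4.1% |
| 15% | 22.1% | 12.5% |
| 20% | 43.1% | 26.1% |

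The need for repeats could be negligible or common, and the documents do not settle which.

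**The case against.** The best defence is that both windows can be carried out. Both sections describe a treatment-free recording, hemofiltration has one weekly gap that holds either length, and a repeat exactly 7 days later returns to that gap. This stands. The defect is that section 2.9a does not state the placement.

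A second defence is that section 2.9 puts the recording at the end of the phase and before the switch, so a site could make the first attempt early enough. That is true, but section 2.9a times the same recording after the first 3 months, and neither section asks for lead time.

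Third, ambulatory pressure is neither the primary outcome nor named among the objectives in section 2.8. The primary analysis in section 2.13 compares pre-dialysis systolic pressure in the last month on each modality. This also stands and limits the consequence.

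A reader might infer a large bias from hemofiltration windows that run through a session. The documents do not support that as the plan's intent, since both sections describe a recording free of treatment, and they give no rate of pressure rise between sessions from which to compute an effect in mmHg.

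**Conclusion.** The point holds as a matter of inconsistent and incomplete specification. Two windows are given for the same recordings. Forty-four hours is the usual between-treatment gap on hemodialysis only, and under 6-day hemofiltration either window needs the one weekly off-day gap. The 7-day repeat is not protected from falling after a change of modality, for the middle recording in all patients and for the randomization recording in those starting hemofiltration.

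Two stronger statements should not be made. One is that repeats will fall on the wrong modality. That follows from the literal timing in section 2.9a, but not if the first attempt is early enough or the switch waits. The other is that repeats will be analysed under the previous modality. The protocol says nothing about how a repeat is labelled.

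The primary outcome is unaffected. The gap figures assume a constant session hour and the hemofiltration schedule in section 2.9. Amendment #4 states no schedule for daily hemodialysis, so the gaps cannot be computed for that arm and must be rechecked. The correction should be made, since it is cheap and prevents recordings on the wrong modality in a small trial.

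**What to change.** 1. Reconcile sections 2.9 and 2.9a to one window length, and state the number of readings to which the 75% rule applies. The choice of length is the sponsor's.
2. State one placement rule for both modalities. If the window is to stay treatment-free, the daily arm needs the weekly off-day gap. Recheck this against the daily hemodialysis schedule under amendment #4.
3. Make the first attempt at least about 9 days (44-h window) or 8 days (24-h window) before the change of modality or the end of the study. Alternatively, hold the change until a valid recording is obtained.
4. Analyse any recording by the treatment actually being received when it was made.

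The cost is protocol wording and visit timing, with no extra recordings. With an earlier first attempt, the recording falls slightly before the end of the period. Holding the change instead would lengthen the period for patients who need a repeat.

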**2.9b LABORATORY MEASUREMENTS**

The standard laboratory tests including hemoglobin, electrolytes, bicarbonate (TCO2), calcium, albumin, phosphate, urea and creatinine (Jaffe) will be measured pre hemodialysis/hemofiltration using the Ottawa Hospital Laboratory.

**2.9c EXTRACELLULAR FLUID VOLUME MEASUREMENT BY BIOIMPEDANCE**

For patients on hemodialysis, an increase in extracellular fluid volume is associated with hypertension and left ventricular hypertrophy (84). Tracer dilution techniques are considered the gold standard for the measurement of extracellular water but are complicated and not available in many centres. Additionally, extracellular water assessment by the bromide technique in patients with an expanded extracellular water is problematic due to the uncertainty of the correction constants for plasma water and the Gibbs-Donnan equilibrium (85). Additionally, a number of different clinical assessment tools have been used to estimate a patient’s hydration status including physical examination, blood volume monitoring and inferior vena cava measurement, but they either do no correlate well with direct measures of extracellular fluid volume and/or cannot be used to track sequential changes in volume status (86-90). However, bioelectrical impedance technology offers the potential to directly assess extracellular fluid volume, intracellular fluid volume and total body water. The technology is based on the ability to detect differences in the conductive properties of a cell by measuring its resistance (impedance) to electrical current. At low frequencies, the current cannot cross cell membranes and hence is only flowing through the extracellular fluid volume. At high frequencies, the current flows through the extracellular fluid volume and intracellular fluid volume. The technique is reliable for tracking sequential changes in extracellular fluid volume (r=0.95 between measurements on two separate days, 85).

For the purposes of this study, post treatment extracellular fluid volume will be measured 3 times; at the time of randomization, after the first 3 months of the cross-over phase and again at study completion using the Xitron Hydra (Xitron Technologies, San Diego, CA). The Hydra is a multifrequency bioimpedance analyzer that allows for differentiation of extracellular fluid volume and intracellular fluid volume. Four electrodes will be placed on the wrist and ankle on the non-fistula side. The measurement will take place 20 minutes after completion of the hemodialysis or hemofiltration treatment to allow for plasma re-filling. Previously the coefficient of variation of the method and intra-observer error were 2.5% (91). One of the investigators (DZ) will obtain expertise in the technique with the assistance of [name] at the University Health Network, Toronto, Ontario.

**2.9d SYMPATHETIC NERVE ACTIVITY**

As previously described by the co-applicant (MR), postganglionic multifibre muscle sympathetic nerve activity will be recorded microneurographically using a sterile tungsten microelectrode with a shaft diameter of 200 μm and a non-insulated tip of 5 μm in diameter inserted into a muscle fascicle of the peroneal nerve posterior to the fibular head. A reference electrode is inserted subcutaneously 1 – 2 cm from the recording electrode. Electrodes will be connected to the remote, low noise preamplifier of the Nerve Traffic Analyzer, (University of Iowa, Iowa City, Iowa). The neural signal will be amplified by 40,000, input to a bandpass filter (0.5 to 1 KHz) and integrated to obtain a mean voltage neurogram. The mean voltage neurogram, ECG, respirations and BP signals will be digitized with a sampling frequency of 2,000 to 5,000 Hz, and recorded on a Ponemah Data Acquisition System (Gould, Valley View, OH). Pulse synchronicity and low signal-to-noise ratio will confirm burst activity as being of muscle sympathetic efferent origin. MSNA (burst/min and bursts/100 beats) will be calculated from 10-minute recordings after 20 minutes of rest. Muscle sympathetic nerve activity recordings will be performed at the time of randomization, after the first 3 months of the cross-over phase and again at study completion when the patient is at their dry weight.

**2.10 What is the proposed sample size?** 20 patients. Based on our previous pilot study, assuming a standard deviation of 11, an alpha = 0.05, we will have 80% power to detect a difference of 11 between the groups.

**2.11 Planned recruitment rate –** Patients will be recruited from the ~ 600 patients undergoing in-centre hemodialysis at the Ottawa Hospital. Due to limited access to the machines for hemofiltration a maximum of 10 patients can be treated in each 6 month period. Allowing for upfront recruitment and training time, it is anticipated that it will take 18 months to recruit all of the patients with a further six months after the last patient is recruited to complete the study. Data analysis and manuscript preparation are expected to take an additional 6 months.

**2.12** **Anticipated compliance and loss to follow-up problems –** Reported drop out rates from daily dialysis programs are low. In our own home hemodialysis program, only 1 patient out of 20 has chosen to return to conventional hemodialysis after completing training. In our one-month pilot study of daily hemofiltration, one patient dropped out of the study due to an adverse event. Given the longer duration of follow-up and the requirement for an in-centre protocol, we anticipate 2 patients may drop out of the study. Furthermore, we don’t anticipate any loss to follow-up as end stage renal disease patients require dialysis as a life saving procedure. However, patients may decide to withdraw from the study.

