**2.4 Methods for protecting against sources of bias**

Patients cannot be blinded to the hemofiltration modality. However, the final data analysis will be by individuals who are blinded to the patient’s therapy. Nurses who are unaware of the objectives of the study will take vital signs with an automated blood pressure cuff. Ambulatory blood pressure monitoring and muscle sympathetic nerve activity recordings are unlikely to be affected by patient knowledge of treatment modality.

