**2.13 Proposed type of analysis**

The primary analysis, using a t-test, will be a comparison of mean pre-dialysis systolic blood pressure values from the last month on hemodialysis and the last month on hemofiltration. As described by Zoccali et al, this will give us an assessment of the pressure load as experienced by the left ventricle (92). Supporting analytic and descriptive analysis will be carried out to ensure Consort guidelines can be followed for publication of results.

Continuous outcomes measures for the secondary analysis will be analyzed in exactly the same manner. All efforts will be made to minimize missing values. A sensitivity analysis under extreme but reasonable assumptions will be carried out to evaluate the impact of any missing values.

Lastly, linear regression will be undertaken with systolic pressure as the dependent variable. Treatment type, extracellular fluid volume and sympathetic nervous system activity will be examined for their independent effects on blood pressure control.

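### Section 2.9d states the burst-acceptance rule the wrong way round: it asks for a low signal-to-noise ratio where only a high one can confirm a sympathetic burst

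*Protocol*

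**What the plan says.** Section 2.9d describes microneurography of the peroneal nerve and gives one rule for recognising bursts: "Pulse synchronicity and low signal-to-noise ratio will confirm burst activity as being of muscle sympathetic efferent origin". Both nerve-activity measures rest on the bursts so accepted: "MSNA (burst/min and bursts/100 beats) will be calculated from 10-minute recordings after 20 minutes of rest". Each patient is recorded three times: at randomization, after the first three months of the cross-over, and at study end. The same section describes equipment meant to keep noise down: "Electrodes will be connected to the remote, low noise preamplifier of the Nerve Traffic Analyzer", followed by a bandpass filter. It presents the technique as established: "As previously described by the co-applicant (MR), postganglionic multifibre muscle sympathetic nerve activity will be recorded microneurographically".

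Section 2.8 names sympathetic activity as one of two candidate mechanisms in the first secondary objective. Section 2.13 uses it in a linear regression for systolic pressure: "Treatment type, extracellular fluid volume and sympathetic nervous system activity will be examined for their independent effects on blood pressure control".

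On bias, section 2.4 says that "muscle sympathetic nerve activity recordings are unlikely to be affected by patient knowledge of treatment modality". It also says that the closing analysis will be done by people blinded to therapy. It does not say who identifies the bursts or whether that step belongs to the blinded analysis.

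**The concern.** A signal-to-noise ratio compares the size of the neural signal with the background. When it is low, a burst and a random fluctuation look alike. Making "low signal-to-noise ratio" a condition for calling a deflection a true burst therefore runs against what the criterion is for.

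This is more than loose description. It is the protocol's only written rule for accepting bursts, so both the per-minute and the per-100-beats counts depend on it. If operators follow it, the count is wrong. If they ignore it, as is likely, no valid written rule on signal quality governs the three visits, and consistency between electrode insertions rests on unrecorded judgement.

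The measurement is a costly one for the patient. It needs three needle recordings, and section 2.9 has certain antihypertensive classes weaned because they affect it. The part of section 1.3b on the causes of hypertension calls microneurography the one direct method and says that plasma norepinephrine studies have been inconclusive. The serum catecholamines added by amendment #2 are thus a support and not a replacement.

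A second, smaller gap sits beside this one. Deciding what is a burst involves judgement, the trial is unblinded, and section 2.4 deals only with what the patient knows.

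**Working it through.** The protocol gives no figure to reproduce: section 2.9d states no threshold, and the sample size, alpha and power do not bear on the direction of a criterion. The check is a logical one.

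**Step 1. Read the rule as written.** Two conditions are joined by *and*: the deflection is pulse-synchronous, and its signal-to-noise ratio is low. Compare this with the same rule requiring a high ratio.

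| Deflection | Rule as written | Rule with a high ratio |
| --- | --- | --- |
| Pulse-synchronous, high ratio | rejected | accepted |
| Pulse-synchronous, low ratio | accepted | rejected |
| Not pulse-synchronous, high ratio | rejected | rejected |
| Not pulse-synchronous, low ratio | rejected | rejected |

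The two versions agree on everything that is not locked to the pulse. They disagree on both pulse-synchronous rows, and there the written rule gives the opposite answer each time. The same holds if the ratio is taken as a property of the whole recording: a clean recording would fail and a poor one would pass.

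**Step 2. Compare with the rest of section 2.9d.** A low-noise preamplifier and a bandpass filter serve to raise the signal-to-noise ratio. A rule that then asks for a low ratio conflicts with the set-up in the same paragraph. Nothing elsewhere in the protocol, including the four amendments, corrects the sentence.

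**Step 3. Follow the outcome through.** Accepted bursts give the two nerve-activity measures, which serve the first secondary objective and enter the section 2.13 regression. The primary analysis does not use them: "The primary analysis, using a t-test, will be a comparison of mean pre-dialysis systolic blood pressure values". The sample size in section 2.10 is not built on them either.

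**Step 4. Count what is exposed.** Three recordings in each of 20 patients give at most 3 × 20 = 60. If the two drop-outs anticipated in section 2.12 occur, 18 patients give 3 × 18 = 54 recordings in complete sets.

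**Step 5. Ask whether the error can be sized.** Under the literal rule, clean bursts are lost, which lowers the count, and weak pulse-locked activity is admitted, which raises it. The net change depends on the mix of the two in each recording. The protocol gives no burst rate, heart rate or recording quality from which to work it out, so neither its size nor its sign can be derived.

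**Step 6. Check who counts.** Section 2.9d has the signals digitised and stored, so counting could be done offline by the blinded analysts of section 2.4. The text neither says so nor rules it out.

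**The case against.** The strongest reply is that this is a one-word slip. The low-noise equipment and the reference to a technique already described by a co-applicant show what was meant. A trained operator would not discard every clean recording, and a numerical cut-off is ordinary laboratory detail that a protocol need not carry. Most of this stands. It makes literal use unlikely and keeps the point small. It does not make the sentence right, and no other text puts it right.

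A reader might go further and infer that noise in general would be counted as bursts. The document does not support that. Pulse synchronicity must also be met, so noise that is not locked to the pulse is still excluded; only weak activity that coincides with the pulse gets through.

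A reader might also infer that burst counts would be inflated by some stated percentage. Any such figure needs an assumed burst rate, heart rate and false-acceptance rate, none of which the protocol gives. A sum that keeps all true bursts and adds false ones describes a lenient threshold, not a reversed one.

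Finally, a reader might conclude that the person counting knows the modality. That is not established: the blinded analysis may include counting. The sentence in section 2.4 about patient knowledge is not wrong in itself; it simply does not address the reader of the recording. Differences in recording quality between insertions have no stated link to modality either, so they would be expected to add scatter and not a bias in a known direction.

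**Conclusion.** The point holds as an error of direction in an operative rule. As written, section 2.9d rejects clean pulse-synchronous bursts and accepts only weak activity that coincides with the pulse, in conflict with its own recording set-up. It is probably a slip. Its reach is the secondary nerve-activity outcome and the regression containing it; the primary comparison and the sample size are untouched. Up to 60 recordings fall under the rule, but the effect on the counts cannot be sized from the document.

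This conclusion rests on the ordinary meaning of signal-to-noise ratio and on reading the two conditions as joint. On blinding, the finding is only that the protocol leaves the burst reader's status unstated.

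**What to change.** - In section 2.9d, require pulse synchronicity and a high signal-to-noise ratio, at or above the laboratory's own minimum. Set that minimum before the first recording and apply it unchanged at all three.
- In section 2.4 or 2.9d, state that bursts are counted from digitised files coded to hide patient, visit and modality.

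The cost is one corrected sentence, one added sentence and coded file names, since the signals are already to be digitised and stored. The downside is that a few recordings below the minimum may become missing, which matters somewhat with 20 patients; the sensitivity analysis for missing values in section 2.13 can cover them.

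The correction itself does not depend on the minimum or the coding. Those two additions are inexpensive protection for a judgement-based outcome in an unblinded trial.
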